The study also has an active reference arm of adalimumab treatment, an approved anti-TNF $\alpha$  drug; however, no formal comparison of sonelokimab vs adalimumab is planned. Alongside the placebo arm, the adalimumab reference arm will be used to calibrate this study's patient population as compared to other clinical programs. After Week 12, participants receiving adalimumab not achieving at least a 20% improvement in baseline tender and swollen joint count will switch to sonelokimab 120 mg Q2W. This change in study treatment will allow initial assessment of the response to sonelokimab in anti-TNF $\alpha$  non-responders.

Inclusion and exclusion criteria have been developed to ensure a well-defined population where efficacy can be determined without introducing any unacceptable risks or confounding effects. The study design incorporates frequent visits and evaluations to optimize assessment of endpoints and collection of safety data.

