### 12.3.1 General Considerations

For continuous variables, descriptive statistics (number of observations, mean, SD, minimum, first quartile, median, third quartile, maximum, and 95% CI, as appropriate) will be given. Categorical variables will be presented as counts and percentages with non-missing values in each category. The count of missing observations will be provided in all descriptive tables. For all statistical analyses, p-values and 95% CIs will be given.

For Part A, descriptive statistics will be presented by 5 treatment arms and by visits from Week 0 to Week 12:

- Arm 1: sonelokimab 120 mg Q2W;
- Arm 2: sonelokimab 60 mg Q2W;
- Arm 3: sonelokimab 60 mg Q4W;
- Arm 4: placebo;
- Arm 5: adalimumab 40 mg Q2W.

For Part B, descriptive statistics will be presented by 9 treatment arms and by visits from Week 0 to Week 24 and repeated by visits from Week 12 to Week 24:

- Sonelokimab 120 mg Q2W→sonelokimab 120 mg Q4W;
- Sonelokimab 120 mg Q2W→adalimumab 40 mg Q2W;
- Sonelokimab 60 mg Q2W→sonelokimab 60 mg Q4W;
- Sonelokimab 60 mg Q2W→sonelokimab 120 mg Q4W;
- Sonelokimab 60 mg Q4W→sonelokimab 60 mg Q4W;
- Sonelokimab 60 mg Q4W→sonelokimab 120 mg Q4W;
- Placebo→sonelokimab 120 mg Q4W;
- Adalimumab 40 mg Q2W→adalimumab 40 mg Q2W;
- Adalimumab 40 mg Q2W→sonelokimab 120 mg Q2W.

Baseline values will be defined as the last non-missing measurement prior to first dose of study treatment.

Change from baseline will be defined as the post-baseline visit value minus the baseline value.

All sensitivity analyses will be regarded as exploratory and no formal adjustment for multiplicity will be made. Details on sensitivity and planned subgroup analyses will be provided in the SAP.

All analyses will be performed using SAS® Software version 9.3 or later.

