| Compliance                                      | Compliance (%) = 100 * (number of visits with treatment received/ number of visits with treatment planned) during the participant's participation in the study.
Compliance is calculated for Part A, Part B and Part A+B using the number of visits with treatment received during the respective Part and planned number in each Part also. |
| Baseline Derivations                     |                                                                                                                                                                                                                                                                                                                                                 |
| Baseline definition                             | Baseline will be defined as the last non-missing measurement prior to first dose of study medication in Part A For baseline characteristics table, if a subject is randomized and not treated then the latest record will be defined as the baseline.                                                                                           |
| Baseline definition for ADA                     | The last sample prior to the first dose of sonelokimab                                                                                                                                                                                                                                                                                          |

|                                                                                                        |                                                          |
|--------------------------------------------------------------------------------------------------------|----------------------------------------------------------|
| Change from baseline                                                                                   | The value at each time point minus the value at baseline |
| Other Derivations                                                                               |                                                          |
| Definition for the derived efficacy parameters are given in the respective efficacy analysis sections. |                                                          |

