- Sonelokimab 120 mg Q2W→sonelokimab 120 mg Q4W;
- Sonelokimab 120 mg Q2W→adalimumab 40 mg Q2W;
- Sonelokimab 60 mg Q2W→sonelokimab 60 mg Q4W;
- Sonelokimab 60 mg Q2W→sonelokimab 120 mg Q4W;
- Sonelokimab 60 mg Q4W→sonelokimab 60 mg Q4W;
- Sonelokimab 60 mg Q4W→sonelokimab 120 mg Q4W;
- Placebo→sonelokimab 120 mg Q4W;
- Adalimumab 40 mg Q2W→adalimumab 40 mg Q2W;
- Adalimumab 40 mg Q2W→sonelokimab 120 mg Q2W.
- Total sonelokimab (safety tables only)

**Part A+B:** For Part A+B no statistical testing will be performed. Summary statistics will be based on the data collected from the visit Week 0 to Week 24. Part A+B tables will only be presented for adverse events.

Unless otherwise stated, the summary statistics will be presented for the following treatment groups:

- Placebo (Part A only)
- Total Sonelokimab 120mg
- Total Sonelokimab 60mg
- Total Adalimumab 40mg Q2W
- Total Sonelokimab

For the total groups they will have different subjects potentially for Part A and Part B and subjects will only have results shown for the Part when they took the relevant treatment.

All participant data, including those derived, will be presented in individual participant data listings. Unless otherwise stated, unscheduled visit results will be included in date/time chronological order, within participant listings only. All listings will be sorted by treatment group, investigational site, participant number, date/time, and visit. The treatment group as well as participant's sex, age and race will be stated on each listing. Unless otherwise stated, safety data listings will be based on SAF and efficacy data listings will be based on FAS.

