## 8.9.1 Adverse Events

All AEs will be classified by Primary SOC and PT according to MedDRA Version 25.0 or higher and will be graded according to the National Cancer Institute Common Terminology Criteria for Adverse Events (NCI CTCAE) version 5.0.

AEs will be summarized by SOC and PT using counts and percentage (i.e., number and percentage of participants with an AE). AEs will be sorted by decreasing frequency within each SOC and PT as per the overall column.

Where a participant has the same AE, based on PT reported multiple times, the participant will only be counted once at that PT level. Where a participant has multiple AEs within the same SOC, the participant will only be counted once at that SOC level.

If a participant experiences the same AE more than once with different severity grades, then the event with the highest severity will be tabulated by maximum severity. In addition, AEs with a missing severity will be presented in the summary table under the category of ‘Missing’ and will not be imputed.

TEAEs are defined as any AE occurring or worsening on or after the first dose of study treatment.

TEAEs will be assigned to Part A, Part B and Part A+B using the event start date and time and will be defined as:

- Part A: events started on or after the first dose of study medication for Part A but not after Part B or events present prior to the first dose of study medication for Part A but increased in severity on or after dosing on Part A but not after Part B
- Part B: events started on or after the first dose of study medication for Part B or events present prior to the first dose of study medication for Part B but increased in severity on or after dosing on Part B

For Part A+B treatment emergent AEs relating to the Part when the subject was on the corresponding treatment are considered as TEAE.

Adverse events with an onset on Day 1 which are based upon pre-dose lab tests will be considered as not treatment emergent. These are defined as:

- Adverse events which begin on study day 1 with SOC = “Investigations” or PT in (“Hypercholesterolaemia” “Hyperlipidaemia” “Dyslipidaemia”, “Type V hyperlipidaemia”).
- The latest lab test taken on Day 1 has a time which is before the treatment start time.

Treatment-related AEs are those events with relationship to study drug ‘Related’ as recorded on the CRF. If the relationship to study drug is missing, the AE will be considered as treatment related.

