### 8.9.2 Clinical Laboratory Evaluations

All central laboratory (hematology, biochemistry, urinalysis) parameters will be collected as described in [Appendix I](#).

Observed and change from baseline values for clinical laboratory parameters will be summarized using descriptive statistics by treatment group and visit separately for Part A and Part B. Shift from baseline to each scheduled assessment and the worst post treatment value according to normal ranges criteria will be presented. Shift from baseline to each scheduled assessment and the worst post treatment value according to CTCAEv5.0 criteria will also be presented. CTCAEv5.0 criteria are described in [Appendix L](#). Participants meeting any grade 3 criteria will also be listed.

In addition, the number and percentage of participants meeting the criteria for normal ranges in laboratory parameters will be summarized by treatment group separately for Part A and Part B.

Laboratory results together with the normal ranges will be listed, flagging values that are below or above the normal range. Serum/urine pregnancy tests assessments will be listed only.

Boxplots of the observed and change from baseline values for all clinical laboratory parameters will be presented by treatment group and visit for Part A and Part B. Reference lines for the normal ranges, that consistent across all participants being presented, will be displayed.

For participants with an AE of grade 3 or higher the hematology and chemistry lab parameters for that participant will be presented in a panel plot with a panel for each lab parameter. The x-axis will be the study week and the y-axis will be the absolute lab value.

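### Part B laboratory, vital-sign and ECG tables use only the Week 0 baseline, so for participants who change drug at Week 12 they mix abnormalities from the previous treatment with those of the new one

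*Combined protocol and SAP*

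**What the plan says.** SAP 7.1 gives one general rule: "Baseline will be defined as the last non-missing measurement prior to first dose of study medication in Part A". Protocol 12.3.1 has the same rule: "Baseline values will be defined as the last non-missing measurement prior to first dose of study treatment". Change is then "The value at each time point minus the value at baseline". Nothing in either document defines a baseline at the start of Part B for laboratory, vital-sign or ECG data.

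Two data types have a different reference point. For ADA the baseline is "The last sample prior to the first dose of sonelokimab", which moves to Week 12 for someone who starts sonelokimab in Part B. For adverse events, SAP 8.9.1 counts towards Part B events that start after the first Part B dose, and "events present prior to the first dose of study medication for Part B but increased in severity on or after dosing on Part B".

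The Week 0 baseline carries into these Part B safety displays:

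- SAP 8.9.2 (laboratory): "Shift from baseline to each scheduled assessment and the worst post treatment value according to normal ranges criteria will be presented", with a parallel CTCAE-graded version.
- SAP 8.9.3 (vital signs): counts of participants whose systolic pressure or heart rate moves by at least 20, diastolic pressure by at least 15, or weight by at least 7% from baseline.
- SAP 8.9.5 (ECG): QTc change categories above 30 and above 60 ms, and PR and QRS criteria that include a rise of at least 25%.

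SAP 8.1 bases Part B summaries on the Week 12 to Week 24 visits, in nine sequence columns (for example "Placebo→sonelokimab 120 mg Q4W") plus a Total sonelokimab column for safety tables.

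**The concern.** Three of the nine sequences change drug at Week 12. For these participants a change from Week 0 spans two treatments. A liver-enzyme rise that began on adalimumab and persisted would appear as a Part B shift in the adalimumab-to-sonelokimab column. In the pooled column it would appear simply under sonelokimab.

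The error can also run the other way. If a value falls on the first treatment and returns to its Week 0 level on the second, the change since the switch disappears from the Part B table.

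What is at stake is the descriptive safety profile by drug in Part B, chiefly the pooled column, which is the one most likely to be lifted into a summary of sonelokimab safety. The SAP already judged that adverse events and ADA need a reference point tied to the treatment being described. It gives no reason for treating laboratory, vital-sign and ECG data differently.

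**Working it through.** **The plan's own figure.** The documents give no figure on this point. Their one design figure, power above 80% with 40 per arm, 10% against 40% and two-sided alpha 0.025, reproduces. The standard errors are √(2 × 0.25 × 0.75/40) = 0.0968 under the null and √((0.24 + 0.09)/40) = 0.0908 under the alternative. Power is then Φ((0.30 − 2.241 × 0.0968)/0.0908) = 82.0%. It concerns Part A and does not depend on anything below.

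**1. What a change from Week 0 contains.** For any participant, (W24 − W0) = (W12 − W0) + (W24 − W12). In a drug switcher the first term belongs to the previous treatment.

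**2. Where a reader can undo this.** For a mean change with the same participants at both visits, subtracting the Week 12 row leaves the Part B part.

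**3. Where a reader cannot.**

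- *Shift tables.* Suppose n participants in a sequence are normal at Week 0, a are high at Week 12 and b are high at Week 24. The number newly high since the switch lies anywhere from max(0, b − a) to min(b, n − a). With a = b that is from none to min(a, n − a). The two Week 0 shifts do not determine it.
- *Worst value.* Part B summaries include the Week 12 visit, which protocol 8.3.3 also makes the last Part A assessment. As written, a value taken before the switch can itself be the Part B worst value.
- *Threshold counts.* Take 100 kg at Week 0, 105 kg at Week 12 on placebo and 107 kg at Week 24 on sonelokimab. The change from Week 0 is 7/100 = 7.0%, which meets the criterion; from Week 12 it is 2/105 = 1.9%, which does not. Conversely, 100 kg, then 93 kg, then 100 kg is 0% from Week 0 but 7/93 = 7.5% from Week 12.

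**4. How many participants.** Inputs are 40 per arm (SAP 5.5) and the allocation table (SAP 3.3). All of Arm 4 and the Week 12 non-responders of Arms 1 and 5 change drug. The documents do not give the non-response share r, so the whole range is shown, with r taken as equal in Arms 1 and 5.

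| r | Drug switchers, 40 + 80r (of 200) | From placebo or adalimumab in pooled Part B sonelokimab column, 40 + 40r (of 160) |
|---|---|---|
| 0 | 40 (20%) | 40 (25%) |
| 0.3 | 64 (32%) | 52 (32.5%) |
| 0.5 | 80 (40%) | 60 (37.5%) |
| 1 | 120 (60%) | 80 (50%) |

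The 160 is Arm 1 responders 40(1 − r), Arms 2 and 3 (80), Arm 4 (40) and Arm 5 non-responders 40r. If the shares differ, r1 in Arm 1 and r5 in Arm 5, the fraction is (40 + 40r5)/(160 + 40(r5 − r1)). Its extremes are still 25% (both 0) and 50% (both 1). These counts assume that everyone enters Part B. SAP 3.1 ends treatment at Week 12 for US participants, so actual numbers will be lower.

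**5. Whether efficacy should be re-baselined too.** This was checked by simulating 300,000 participants with no true change and lognormal error on tender and swollen counts at Weeks 0, 12 and 24. The error CV (20–40%) and the correlation between the two counts' errors (0.3–0.6) are assumptions. The share with a spurious 20% reduction in both counts at Week 24 was about:

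- 7–21% from Week 0 with no selection;
- 6–15% from Week 0 among Week 12 non-responders;
- 8–25% from Week 12 among the same non-responders.

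Selection on a poor Week 12 visit therefore does not inflate response measured from Week 0. Moving the reference to that visit does.

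**The case against.** The strongest reply is that nothing is hidden. The sequence columns name both drugs, the Week 12 row is in the table, and observed values accompany changes for laboratory, vital-sign and ECG data. All participant data are listed and Part B has no testing. This is right for mean changes in the nine sequence columns, where mixed is the accurate word and credited to the new drug would be too strong. It does not answer the shift, worst-value and threshold displays, or the pooled column, which names no earlier treatment.

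Three stronger inferences are tempting, and the documents do not support them.

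- *That the Part B efficacy results are misattributed and need a Week 12 baseline.* Protocol 8.9 says of the adalimumab non-responders: "This change in study treatment will allow initial assessment of the response to sonelokimab". A change from Week 0 does mix in what was gained on adalimumab. But the response endpoints are defined against baseline, and the combined NRI/LOCF analysis keeps a switcher's Week 12 result under the Part A arm. Re-baselining joint counts at the visit used to select non-responders would add regression to the mean.
- *That splitting the placebo sequence by Week 12 response would show how much improvement is regression.* Every placebo participant starts sonelokimab 120 mg Q4W at Week 12. That subgroup's later change would be regression plus drug effect, and it could not separate the two.
- *That the main results are affected.* The primary and key secondary analyses stop at Week 12 and do not use Part B data.

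**Conclusion.** The point holds for Part B safety displays that cannot be decomposed: laboratory shifts and worst values, vital-sign and weight change thresholds, and ECG interval change criteria, in the three drug-switch sequences and in the pooled sonelokimab column. Under planned numbers this concerns 40 to 120 of 200 participants, and 25% to 50% of the pooled column. Both ranges assume 40 per arm, full entry into Part B and an unknown Week 12 non-response share, and both are upper figures because US participants do not continue. How many abnormalities would be moved or hidden cannot be estimated from the documents.

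This is a cheap improvement to descriptive safety reporting. It is not a flaw in the efficacy analysis, and it changes no sample size, power or alpha.

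**What to change.** In SAP 7.1, add a Part B safety baseline: the last non-missing laboratory, vital-sign, weight or ECG value before the first Part B dose. Tie it to the date and time of that dose and not to the analysis window. The Week 12 ECG window runs to Day 148, well past the switch, and under protocol 8.6 a missed Week 12 visit moves the first Part B dose to Week 14.

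In SAP 8.9.2, 8.9.3 and 8.9.5, for the three drug-switch sequences and the pooled Part B sonelokimab column, present shift, worst-value and change-threshold tables from that baseline alongside the Week 0 versions. Restrict the Part B worst value to measurements after the first Part B dose. Label each pooled table with the baseline used.

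Keep Week 0 for ACR, PASI and the other efficacy endpoints. If a Week 12 to Week 24 efficacy change is shown for switchers, mark it supplementary and state that regression to the mean is expected in a group selected on its Week 12 joint counts.

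The cost is SAP wording and a few additional descriptive tables. No new data are needed: laboratory tests, vital signs, weight and ECG are all scheduled at Week 12.

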## 7.2 Visit Windows

Visit windows will be used for all scheduled assessments. To allow for unscheduled and discontinuation assessments, the data will be summarized using the assessment (whether reported as a scheduled or unscheduled visit) closest to the nominal visit date, calculated from the first day of dosing. The visit result will be missing if no assessment was reported within the specified visit window around the scheduled date. If two assessments are equidistant from a scheduled visit, the earlier of the two will be used.

The visit windows will be calculated by bisecting the scheduled visit assessments. The upper limit of each window will be the mean of the two adjacent planned study days, rounded down to the nearest integer. The lower limit of each window will be the upper limit of the preceding window plus one, except for the first post-treatment visit which will start at 2.

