### **8.3.3 Week 12 Visit**

Assessments at Week 12 are both the final assessments for Part A and the first assessments for Part B. The dose administered at Week 12 is the first dose for Part B. The last dose administration is scheduled for Week 22.

At Week 12 (at the beginning of Part B) TJC68 and SJC66 response will be assessed in all participants. A responder is defined as a participant who achieves at least a 20% reduction in each of TJC68 and SJC66 assessments at Week 12 compared with baseline. A non-responder is defined as a participant who does not achieve at least a 20% reduction in each of TJC68 and SJC66 assessments at Week 12 compared with baseline.

Treatment assignments in Part B will be allocated based upon response at Week 12 via the IRT as indicated in [Figure 1](#) and described in Section [10.1](#).

In the event a participant does not attend Week 12, please refer to Rescheduling Visits in Section [8.6](#).

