#### **8.6 Rescheduling Visits**

If any visit has to be rescheduled, subsequent visits will follow the original visit date schedule. Visits can take place on the scheduled day  $\pm 2$  days. If a visit is unavoidably delayed outside of this window, it may be rescheduled up to Day +7 after approval by the medical monitor.

The activities performed at the rescheduled visit are to be those activities scheduled for the visit that was delayed, including the administration of any study treatment, as applicable

If a visit cannot take place by Day +7 then the visit should be skipped and the dose from the missed visit will not be administered. The participant is to proceed to the next scheduled visit. For further information on missed doses, see Section [10.4](#).

If the Week 12 visit does not take place, the responder/non-responder assessment should be performed at Week 14 and entered into the IRT. The patient will be assigned to the correct treatment arm according to responder/non-responder status and allocated corresponding Week 14 treatment. The Week 12 dose will be recorded as missed.

Doses of study treatment are to be administered at least 7 days apart. Thus, care will be taken to avoid scheduling a visit within 7 days of the previous or next scheduled dose.

Additional unscheduled visits for the purpose of re-testing of laboratory parameters or safety monitoring may be included as deemed necessary by the investigator.

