#### **10.1.1 Sonelokimab**

[figure not shown]

Sonelokimab will be administered by a site-approved, unblinded study treatment administrator. Blinded study personnel will not be in attendance while study treatment is being prepared or administered. Used syringes will be placed immediately out of sight in a sealed sharps container.

In Part A, the 3 sonelokimab treatment arms are as follows:

- Arm 1 (sonelokimab 120 mg Q2W): Sonelokimab 120 mg will be given as SC injection at Weeks 0, 2, 4, 6, and 8. Participants will receive a placebo injection at Week 10 to maintain the blind;

- Arm 2 (sonelokimab 60 mg Q2W): Sonelokimab 60 mg will be given as SC injection at Weeks 0, 2, 4, 6, and 8. Participants will receive a placebo injection at Week 10 to maintain the blind;
- Arm 3 (sonelokimab 60 mg Q4W): Sonelokimab 60 mg will be given as SC injection at Weeks 0, 4, and 8. Participants will receive a placebo injection at Weeks 2, 6, and 10 to maintain the blind.

In Part B, after allocation of responders and non-responders, the sonelokimab treatment arms are as follows:

- Responders from Arm 1, non-responders from Arm 2, non-responders from Arm 3, and participants from Arm 4 will receive sonelokimab 120 mg Q4W until Week 20. Placebo injections will be given at Weeks 14, 18, and 22 to maintain the blind;
- Responders from Arm 2 and responders from Arm 3 will receive sonelokimab 60 mg Q4W until Week 20. Placebo injections will be given at Weeks 14, 18, and 22 to maintain the blind;
- Non-responders in Arm 5 will receive sonelokimab 120 mg Q2W with SC injections at Weeks 12, 14, 16, 18, and 20. Participants will receive a placebo injection at Week 22 to maintain the blind.

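### The Week 12 efficacy windows have no cut-off at the first Part B dose, so for a few non-US participants a post-crossover record can stand as the Part A Week 12 result

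*Combined protocol and SAP*

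**What the plan says.** Protocol 8.3.3 gives the Week 12 visit two roles: "Assessments at Week 12 are both the final assessments for Part A and the first assessments for Part B". It adds that "The dose administered at Week 12 is the first dose for Part B". In Part B, "participants from Arm 4 will receive sonelokimab 120 mg Q4W until Week 20" (Protocol 10.1.1), and non-responders in Arms 1 and 5 change drug (Protocol Table 3). SAP 3.1 limits Part B to non-US participants; US participants finish treatment at Week 12.

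SAP 7.2 assigns records to visits by study day, counted from the first dose. It fills each visit "using the assessment (whether reported as a scheduled or unscheduled visit) closest to the nominal visit date", and its stated purpose is "To allow for unscheduled and discontinuation assessments". On ties, "If two assessments are equidistant from a scheduled visit, the earlier of the two will be used". With nothing in range, "The visit result will be missing if no assessment was reported within the specified visit window around the scheduled date". A missing binary endpoint then counts as non-response (SAP 7.3.1).

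The Week 12 windows are Day 72 to 92 for the ACR components, Day 72 to 99 for PASI, Day 58 to 99 for SF-36v2 and FACIT-Fatigue, and Day 2 to 127 for BSA and mNAPSI. SAP 8.1 defines Part A data by visit label, Week 0 to Week 12.

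Elsewhere the SAP does split at the first Part B dose: for adverse events (8.9.1), for concomitant medication (8.4.7), and in Appendix K for the observation time of placebo and adalimumab participants.

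**The concern.** The primary and key secondary tests compare randomised arms at the end of a placebo-controlled period. A value taken after a placebo participant has received sonelokimab does not belong to that period. As written, the window rule can do two things:

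- It can prefer a post-dose record over a valid pre-dose one, because it looks only at distance from Day 85.
- It can fill a missing Week 12 item with a post-dose record. The endpoint is then no longer missing, and the participant is not imputed as a non-responder.

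Extra records are foreseeable. Protocol 8.6 provides for "Additional unscheduled visits for the purpose of re-testing of laboratory parameters" and for safety monitoring. Protocol 8.7 allows repeat measurements and any assessment the investigator considers necessary. Protocol 8.3.4 places an EOT visit, which includes PASI and BSA, at the time of early discontinuation.

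**Working it through.** **1. Window limits.** SAP 7.2 sets the upper limit at the mean of the two adjacent planned days, rounded down. The planned days come from the Schedule of Activities. All stated limits reproduce.

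| Assessment | Next planned day | Upper limit | Days open after a Day 85 dose | After a Day 83 dose |
|---|---|---|---|---|
| ACR components | 99 | (85+99)/2 = 92 | 92−85 = 7 | 9 |
| PASI | 113 | (85+113)/2 = 99 | 99−85 = 14 | 16 |
| SF-36v2, FACIT-Fatigue | 113 | 99 | 14 | 16 |
| BSA, mNAPSI | 169 | (85+169)/2 = 127 | 127−85 = 42 | 44 |

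**2. When a valid Week 12 record is displaced.** Visits may fall within ±2 days, so the earliest is Day 83. A delayed visit may take place up to Day 85+7 = 92. A later record on day t displaces a visit on day v only if |t−85| < |v−85|.

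- v = 83 (distance 2): t = 84, 85 or 86 displaces it. Day 87 ties, and the earlier record stands.
- v = 84 (distance 1): only t = 85 displaces it. Day 86 ties.
- v = 85 to 92: nothing later displaces it.

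**3. When a missing item is filled.** If the Part B dose was given but an item was not obtained at Week 12, the closest record in the window is used. Post-dose records qualify up to Day 92, 99 or 127, according to the item.

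**4. Routine visits.** Week 14 (Day 99±2 = 97 to 101) lies outside the ACR window, and PASI is not scheduled at Week 14. If the whole Week 12 visit is missed, the first Part B dose moves to Week 14 (Protocol 8.6), so records before that dose are not post-crossover.

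**5. Size per participant.** ACR50 has 40 per arm: 1/40 = 2.5 points. The PASI90 subgroup is expected to be 50% to 67% of the FAS: 0.50×40 = 20 and 0.67×40 ≈ 27 per arm, so one participant is 1/27 = 3.7 to 1/20 = 5.0 points.

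**6. Power illustration.** The plan's figure is reproduced first, from 10% v 40%, n = 40 per arm and two-sided alpha 0.025. Power = Φ{[0.30√40 − 2.2414√(2×0.25×0.75)] / √(0.10×0.90 + 0.40×0.60)} = Φ{(1.897 − 1.373)/0.574} = 82.0%, which agrees with the stated figure of more than 80%.

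Now suppose a fraction f of placebo ACR50 results is taken after crossover, with response rate q. The placebo rate becomes 0.10(1−f) + qf. The documents give neither f nor q; both are assumptions.

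| f (participants of 40) | q = 20%: placebo rate, power | q = 40%: placebo rate, power |
|---|---|---|
| 2.5% (1) | 10.25%, 81.0% | 10.75%, 79.2% |
| 5% (2) | 10.5%, 80.1% | 11.5%, 76.2% |
| 10% (4) | 11.0%, 78.2% | 13.0%, 69.8% |

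The q = 40% column is an extreme. It gives placebo participants, within days of one dose, the rate planned for sonelokimab at Week 12.

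**The case against.** The strongest reply is that the confirmatory endpoints are largely protected already, and much of it stands.

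- Part B treatment is allocated from the joint counts, so under the protocol a Part B dose follows a joint count. Both counts are required for ACR50 and ACR20. A participant with no Week 12 assessment cannot gain an ACR response after dosing by this route.
- What remains for ACR is mainly a single repeated or late component. hs-CRP is one of five, of which three must improve. It changes ACR50 only if both joint counts reach 50% and exactly two of the other four components do.
- Protocol Table 12 lists hs-CRP under blood chemistry, but the Schedule of Activities lists it separately. Whether a chemistry re-test would produce a new hs-CRP value is not stated.
- The days up to Day 92 are needed for Week 12 visits that are properly delayed.

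A reader might go further and infer that every placebo participant is exposed, that the primary endpoint is open for six weeks of Part B, or that the gap favours a false positive finding. The documents support none of these. US participants have no Part B. The 42 days apply to BSA and mNAPSI, which are not confirmatory outcomes (post-baseline BSA enters only minimal disease activity). Post-sonelokimab data in placebo participants would most plausibly raise placebo response.

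The reply does not remove the gap. The rule can replace a valid pre-dose value, and non-responder imputation cannot act where a post-dose record has filled the window.

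**Conclusion.** The point holds within limits. For non-US participants dosed in Part B, SAP 7.2 allows a post-crossover efficacy record to become the Part A Week 12 value in the two situations in steps 2 and 3 of the working. For ACR50 and ACR20 the exposure is mainly one component repeated or collected late, by Day 92. For PASI90 it is an unscheduled or early EOT PASI up to Day 99.

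The documents give no frequency, and the number affected is probably small. In the placebo arm the likely result is dilution. In the sonelokimab arms, bypassing non-responder imputation could raise the response rate, so the net direction is not certain in every case. The per-participant sizes assume that the responder status actually changes. The power table treats whole ACR50 results as post-crossover and so overstates the single-component route. This is a defect in a written rule that should be corrected before the Part A lock, not a threat to the trial's conclusions.

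**What to change.** Add to SAP 7.2, for efficacy assessments only:

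- For participants dosed in Part B, a record after the first Part B dose is not eligible for the Week 12 window or any earlier one.
- A record dated on the day of that dose counts as pre-dose unless a recorded time shows otherwise.
- If no eligible record remains, Week 12 is missing. Non-responder imputation then applies to binary endpoints, and continuous endpoints stay missing under the MMRM.
- The present upper limits stay as they are, for delayed Week 12 visits and for participants who do not enter Part B.

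The SAP should also say that post-dose records left without a window (for ACR components, those before Day 93) appear in listings only.

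The cost is a short paragraph in the SAP and one date condition in the derivation programs. No new data are needed, because the same-day rule works without clock times. Sample size and planned power do not change. Efficacy would then follow the same split that the SAP already uses for adverse events.
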